**Intervention’s key messages: April-August 2020**
Four risk factors for the development of body image concerns were identified: (1) social media and influencers, (2) appearance-based comparisons, (3) appearance-based teasing, and (4) body talk.It was decided to reinforce the positive body image traits throughout the intervention identified during the aforementioned focus groups.
**Mode and format of delivery: April-August 2020**
Storytelling was chosen as the mode of information delivery, as narrative health education is proven to be effective [75] and engaging, even among those with low health literacy [76]. (See Multimedia Appendix 3 for a synopsis of the intervention’s narrative).Videos were chosen as the intervention format to deliver the core messages owing to their efficiency in delivering content information (see Media Richness Theory [77]) and ability to pique an audience’s attention and interest [78].Interactive activities to reinforce the key messages learned during the videos were added to elicit cognitive dissonance, an effective change technique seen throughout the body image intervention literature [79,80].
**Concept creation: August 2020-January 2021**
Two storyboard concepts were considered: time travel and a detective-based storyline. Time travel was selected given the ability of this concept to convey the additive impact of body image concerns to young people.A combination of animated characters and real people was used, as cartoon characters in health intervention studies have been shown to be acceptable to younger and older adolescents [81-83], as is the combined use of cartoon characters and real people [84].The plot and story details were drafted and refined over several collaborative discussions among the various project stakeholders.Body image change techniques (including those based on psychoeducation and media literacy [54]) were embedded within the video narrative.Six time travel–based videos (ie, one for each target risk factor, plus introductory and concluding videos) were drafted using storyboards and basic animation.
**U-Report poll on appearance-based teasing: January 2021**
A second U-Report poll with 240 young women was conducted to provide clarity as to how appearance-based teasing presents among young people in Indonesia.Poll results provided direction on how to address appearance-based teasing, showing that it is prevalent both online and face-to-face, and that teasing toward young women usually comes from other women, either from friends or family members [85].
**Cocreation of videos with the target audience: February 2021**
Findings on rough animated versions of the videos from four online focus groups with young women aged 15-19 years (N=16) showed strong comprehension, acceptability, and enjoyment of the videos.The young women provided direction regarding appropriate terminology to aid comprehension within their age group.
**Casting, scripts, props, sets, filming: February-March 2021**
Detailed scripts were written, casting auditions held, sets and props sourced, and decisions on futuristic details such as makeup and style were decided.Accurate representation of the diverse Indonesian population through the actors and animated characters involved ensuring that various ethnicities, skin shades, hair textures, distinct types of religious dress, body sizes, and regional accents were included.The videos were filmed. Numerous alternative versions were shot for scenes considered potentially problematic for comprehension so that options were available to explore with young women, if necessary.
**Development of activities: February-April 2021**
Activities were developed to allow users to practice the information learned and/or to reflect on their own cognitions and behaviors in light of the video content.The team was guided by Girl Effect and Percolate’s prior experience of disseminating similar interactive content for other health campaigns, as well as the body image scholars’ expertise in effective change techniques.Eliciting cognitive dissonance throughout the activities was prioritized, for example, by asking users to speak out against appearance ideals, challenge body talk, and stand up to those bullying based on appearance.
**Acceptability testing of the complete intervention: April 2021**
Six online focus groups of young women aged 15-19 years (N=36) were conducted to assess intervention acceptability and comprehension, revealing strong acceptability, comprehension, and enjoyment of the videos and activities (see the Intervention Acceptability section).No issues with comprehension were identified, and thus no alternative scenes were required.
**Final intervention edits: May 2021**
Based on focus group feedback, minor edits were made to the instructions for the activities, which focused on making the tone less formal and enhancing comprehension.

**Figure 1 figure1:**
[figure not shown]
The video thumbnails for each of the 6 episodes in *Warna-Warni Waktu*.

**Figure 2 figure2:**
[figure not shown]
Example activities. The activity on the left asks users to identify the differences between an edited and unedited photo (Video 2, Activity 3). The activity on the right asks users to complete the comic strip with a comment about why appearance-based comparisons are unnecessary (Video 3, Activity 2).

Although the majority of the activities are short, four activities are more in-depth, which consist of writing up to 250 words expressively and/or self-compassionately about what they learned in the video, titled “Your Own Words.” These activities were deemed important for participants to complete given the emerging evidence that expressive and compassion-based writing are effective at reducing body dissatisfaction across a range of settings [86,87]. As such, all participants in the trial that complete these activities will be entered into a competition to win Rp50,000 (approximately US $3.50) in mobile phone credit. The responses to this activity will be judged by two authors (KN and BM). Judging will be based upon the best response being (1) relevant, (2) of adequate length, (3) original, (4) potentially inspirational to other young women, and (4) sounding sincere/honest. This approach reflects how the intervention will be disseminated on social media, should the trial find it to be effective (ie, girls who engage with the intervention once disseminated will have the opportunity to submit their response to the writing task for the chance to win Rp50,000 in phone credit). This is a tried-and-tested method to improve engagement in activities that Girl Effect has used in previous health campaigns on social media.

### Intervention Acceptability

In April 2021, the intervention underwent acceptability testing with 36 young women in six focus groups. All groups watched the entire series; however, to minimize participant burden, three groups completed the activities associated with Videos 1-3 and three groups completed the activities for Videos 4-6, providing acceptability feedback on each. The videos scored high on likeability: scores across the videos ranged from 4.44 to 5 (SD 0-0.98) on a 5-point Likert-type scale ranging from 1 (hated the video) to 5 (loved the video). Only one respondent reported not fully understanding one of the videos (Video Five: Be Your Own Best Friend); all other respondents reported full understanding of each video. This finding was corroborated with qualitative feedback from young women, whereby many successfully restated the key messages from each video.

Similar positive findings were found for each of the activities. Across all activities, likeability scores ranged from 4.42 to 4.89 (SD 0.32-0.90) on a 5-point Likert-type scale ranging from 1 (hated the activity) to 5 (loved the activity). The activities were understood by almost all the young women; 94.44%-100% of respondents reported fully understanding each activity. Again, comprehension was further identified through examination of the young women’s qualitative responses to the activities, with the majority of participants responding in a way that exemplified the key messages learned. The authors were particularly keen to understand the likelihood of the target audience to complete the longer Your Own Words tasks. Findings showed that 95% of respondents reported that if they had the time, they would be interested in participating in these tasks.

Based on the acceptability findings, minor edits were made to the reinforcer activity instructions for greater clarity and comprehension. In addition, upon suggestion from the young women, less formal language was adopted to improve engagement. No changes were made to the design or format of the activities.

### Study Setting

The web-based trial will be coordinated by a research agency based in Jakarta, Indonesia. The aim is to recruit young women from across 10 of the largest cities in Indonesia: Balikpapan, Bandung, Jakarta, Makassar, Manado, Medan, Palembang, Pontianak, Semarang, and Surabaya.

### Eligibility Criteria

Inclusion criteria for participation include identifying as a young woman aged between 15 and 19 years (the target age group for the intervention); having their own mobile phone (to ensure participants receive the WhatsApp notifications regarding the study); and accessing Facebook or Instagram daily (so that the sample consists of those who are most likely to access and engage with the intervention when it is disseminated via social media channels in the future). Exclusion criteria include already following the Girl Effect brand (Springster) on any social media site or having ever accessed the Springster website prior to enrolment (to avoid contamination effects); and, if under 18 years of age, not having written consent from a parent or guardian.

### Participant Recruitment and Procedure

The aim is to recruit 1800 young women aged 15-19 years via a local research agency’s recruitment panel (ie, a database containing contact details of those who have previously taken part in research conducted by the agency and have agreed to be contacted with regard to future research), with the aim to recruit an equal number of participants from each age (ie, 15, 16, 17, 18, and 19 years of age). The CONSORT (Consolidated Standards of Reporting Trials) flowchart is provided in Figure 3. Women and men over the age of 40 years will be contacted via telephone and screened for whether they have a daughter within the eligible age range. If the respondent has more than one daughter in the age range, only one will be eligible to avoid possible contagion effects. The daughter who is the best fit in terms of reaching the age quota will be selected. If this does not distinguish which daughter is selected, the daughter with the birth date closest to the date of contact will be selected. If the respondent does not have a daughter between 15 and 19 years of age, the recruiter will enquire if they know another family with a daughter of this age. If so, the recruiter will request the telephone number of that family and contact them. Only one phone number will be requested per call.

**Figure 3 figure3:**
[figure not shown]
Participant flowchart.

Should an eligible daughter be 15-17 years old, the recruiter will read the parental information sheet to the parent. Parents will then be requested to provide verbal consent for their daughter’s participation and verify their identity and daughter’s age. Parents will then answer questions relating to their socioeconomic status on behalf of their daughter before the recruiter requests to speak to the daughter. If the daughter is not present, the recruiter will request a call back. The daughter will then be screened for eligibility and informed verbal assent obtained. Following the call, and provided the daughter is eligible and gives verbal assent, the parental information sheet will be sent to the parent via WhatsApp, with informed parental consent obtained once more, this time written, over WhatsApp. WhatsApp was chosen as it is the most used communication app in Indonesia [88].

Should an eligible daughter be aged 18 or 19 years, a similar pattern of communication will occur. Parents will verify their own and their daughter’s identity and respond to questions regarding the family’s socioeconomic status. Rather than parents providing informed verbal and written consent, this will be completed by the daughters themselves, in the same manner with which it will be completed by parents of those aged 15-17 years. Verification of identities and ages will be achieved through video calls via the presentation of official documentation (eg, National ID card, family registration card, driving license, student ID). Recruitment is anticipated to take 15 days (inclusive of weekends).

All participants will enter the study (ie, complete the baseline assessment survey) on the same day (Day 1). Participants will receive a data package a day prior to this to ensure they have ample mobile phone data to allow them to participate in the study. A link to the baseline assessment hosted on Qualtrics (Provo, UT) will be sent to participants via WhatsApp at 8 AM (UTC +7) on Day 1, along with a unique participant identification number (PIN). Participants will be requested to enter their PIN on the first page of the baseline survey, in order to match participant responses over time. Participants will have 24 hours to complete the baseline assessment; those who have not completed the baseline assessment within the first 8 hours will be sent a reminder message during the early evening of Day 1. Following the 24-hour window, participants who have completed the baseline assessment will be randomized into one of two conditions: the intervention condition or a waitlist control condition. Participants will be alerted on Day 2 to what happens next, depending on which condition they have been randomized. Those randomized to the intervention condition will be informed that they can expect a series of sequential links to be sent to them daily over the following 6 days. Each link will contain one episode of *Warna-Warni Waktu* and its associated activities. The links will again direct participants to Qualtrics, where the intervention has been embedded (see Multimedia Appendix 2). These participants will be requested to engage with the content of those links daily. Those in the control condition will be told that they will be recontacted in 1 week to complete a second assessment.

On the morning of the third day (Day 3), participants in the intervention condition will be sent their PIN and a link to the first video (and associated activity). Again, participants will be requested to enter their PIN on the first page of the link. Participants will complete state measures of body satisfaction and mood before watching the first video in the *Warna-Warni Waktu* series. State measures of body satisfaction and mood will be asked again immediately after the first video. Next, participants will be presented with the activity for the first video. Before exiting the link, participants will be asked to report on the strength of their internet connectivity while watching the video (see the Measures section below). This process is repeated on Days 4-8 for the remaining five videos (and associated activities). Participants will not be sent reminders to view or engage with the content in these links.

On Day 9 of the study (again, in the morning), participants in both conditions will be sent a link to complete the second assessment. As with the baseline assessment, participants will be given 24 hours to complete this assessment, with reminder messages sent to noncompleters after the first 8 hours. The same process will be executed for the third and final assessment, 1 month later on Day 36. Following the third assessment, all participants will be debriefed on the study aims and provided with additional sources of mental health support, as well as a certificate of participation. Participants who complete all three assessments will be rewarded with Rp125,000 (approximately US $8.75) to encourage participant retention. By this point, the responses to the four 250-word writing activities will have been judged, and those who have won will be contacted and will receive their prize. Those in the waitlist control condition will be provided with a link to the *Warna-Warni Waktu* video series on Day 37. Participants in the waitlist control condition will not be assessed for their engagement with the content. Information sheets and the participant debrief document can be found in Multimedia Appendix 4.

### Randomization and Blinding

Participants will be randomized following completion of the baseline survey. Participants will not be blinded due to the nature of the trial design. They will not be told explicitly of their condition but will be made aware on Day 2 (ie, the day after completing the baseline survey) when they will receive the intervention. Randomization and allocation will be performed on an individual level using an automated, web-based randomizer to sequentially allocate participants based on a block design to ensure a balance of participants across conditions. A researcher external to the project will generate the allocation sequence and assign participants to conditions. They will be blinded to participant information and conditions (ie, they will be given a list of participant identification numbers and asked to assign them to Group A or B using the web-based randomizer). Data analysts will be blinded to condition throughout the trial and analysis of the primary and secondary trait-based measures. Blinding of data analysts during state-based analyses is not possible due to the within-group design of this aspect of the trial. Two separate data files will be provided to the statistician to ensure that blinding during analyses of trait measures is retained. Due to the trial design, the research agency and participants will not be blinded to condition.

### Measures

Self-report measures selected for use are presented in Table 1. For hypothesis one, the primary outcome measure, the Body Esteem Scale for Adults and Adolescents (BESAA) [89], was selected as it is the only body dissatisfaction measure to have been validated among young people in Indonesia (unpublished data of the authors KG, NC, SH, KN, BM, LS, and PD, along with statistical consultants [name] and [name], 2021) and evidence that this scale is amendable to change following interventions of similar duration and content [90,91]. Two secondary outcome measures assessing internalization of appearance ideals [92] and trait mood [93] (unpublished data of the authors KG, NC, SH, KN, BM, LS, and PD, along with statistical consultants [name] and [name], 2021) were again selected for similar reasoning. Owing to the lack of a validated assessment tool to assess skin shade satisfaction, a purpose-built measure will be used to assess this. For hypothesis two, single-item measures of body satisfaction and mood will be utilized. Full questionnaires are presented in Multimedia Appendix 5.

Intervention adherence will be measured objectively through dwell time spent on the Qualtrics page that contains the video and via participant responses to the activities. Intervention acceptability will be assessed through six self-report items; these were informed by established acceptability frameworks [96].

**Table 1 table1:** Measures.

Measure		Description	Time assessed
Demographics		Age, country of birth, ethnicity, religion, socioeconomic status, social media usage	T1^a^
Primary outcome: Trait body dissatisfaction		Body Esteem Scale for Adolescents & Adults (BESAA) [89] adapted and validated among adolescents in Indonesia (17 items). Example item: *I like how I look like in photos.* Response options range from strongly disagree to strongly agree. Mean scores range between 1 and 5, with higher scores reflecting higher body esteem.	T1, T2^b^, T3^c^
**Secondary outcomes**			
	Internalization of appearance ideals	Internalization-General subscale of the Sociocultural Attitudes Towards Appearance Scale-3 [92] adapted and validated among adolescents in Indonesia (12 items). Example item: *I compare my body to the bodies of people who are on TV*. Response options range from *strongly disagree* to *strongly agree*. Mean scores range between 1 and 5, with higher scores reflecting higher internalization of appearance ideals.	T1, T2, T3
	Trait mood	The Positive and Negative Affect Schedule for Children [93] adapted for Indonesia. The validation of this scale among Indonesian adolescents is underway. The factor structure will be determined prior to data analysis and reported in the main effectiveness paper.	T1, T2, T3
	Skin shade satisfaction	A purpose-built, single-item, skin shade discrepancy measure will assess skin shade satisfaction. The chart comprises nine skin colors from dark (1) to light (9). Participants are asked to select the shade that most accurately matches their “current skin shade” and the shade that most accurately reflects the skin shade they would prefer (their “ideal skin shade”). The discrepancy between the two will be used as an indicator of skin shade satisfaction, with higher absolute values indicating less skin shade satisfaction. The score ranges from 0 (*satisfied with skin shade*) to 9 (*very dissatisfied with skin shade*). The measure uses colors from The Pantone Skin Tone Guide [94].	T1, T2, T3
	State body satisfaction	A single 101-point visual analog scale [95] will assess the immediate impact of each video on participants’ state body satisfaction (ie, *How satisfied are you with your appearance, right now, in this moment?*). The total score ranges from 0 (*not at all*) to 101 (*very much*). Higher scores reflect greater satisfaction.	Before and after each video
	State mood	A single 101-point visual analog scale [95] will assess the immediate impact of each video on participants’ state mood (ie, *How happy are you, right now, in this moment?*). The total score ranges from 0 (*not at all*) to 101 (*very much*). Higher scores reflect greater positive mood.	Before and after each video
	Intervention adherence	Digital metrics will assess participants’ engagement with the videos and activities, including: (1) percentage of participants who watch each video (determined by the number of participants whose dwell time on the Qualtrics page hosting each video is equal to or longer than the length of the video); (2) percentage of participants who watch all 6 videos (determined by the number of participants whose dwell time on all 6 Qualtrics pages hosting videos is equal to or longer than the length of each video); (3) average number of videos watched; (4) percentage of participants who complete each activity; (5) average number of activities completed; and (6) average length of time spent engaging with the intervention (ie, watching videos and completing activities) over the 6-day period.	Six-day intervention period
	Intervention acceptability	Six items will assess participants’ acceptability of the intervention. Factors include emotive response to the interventions (eg, enjoyment, likability of characters); relevance (eg, age appropriateness, helpfulness, ease of understanding); ease of use (eg, speed and accuracy of responses); and willingness to recommend (eg, how likely the user would recommend the intervention to a friend). Item scores range between 1 (*strongly disagree*) and 5 (*strongly agree*). Higher scores reflect greater acceptability. Only those randomized to the intervention condition will complete these measures.	T2

^a^T1: baseline assessment.

^b^T2: postintervention assessment.

^c^T3: follow-up assessment.

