### The Intervention

The intervention *Warna-Warni Waktu* was developed over a 20-month period, from October 2019 to May 2021. Textbox 2 presents the intervention development steps taken, which involved close collaboration among body image academics, a creative agency, social media specialists, a nonprofit organization, as well as an industry funder. The intervention development team consisted of numerous women with lived experience of Indonesian culture; namely, five of the six core team members from the creative agency (Percolate Galactic) were young Indonesian women between the ages of 25 and 30. The wider team also consisted of two female Indonesian pediatricians (authors KN and BM), who have lived experience of the culture as well as daily contact with young Indonesian women through their work. Finally, the team included an Indonesian Professor of Women’s Studies (LS). Further, the process involved three rounds of feedback from young Indonesian women at various stages of development to create an intervention that is both for, and created with, young Indonesian women. The final intervention comprises 6 videos between 4 and 5 minutes each (see Figure 1) and 18 interactive reinforcer activities, ranging from approximately 2 to 10 minutes each in length (see Figure 2 for examples). All content is delivered to young women in Bahasa Indonesia, the official language of Indonesia. The activities encourage the target audience to reflect and apply the learnings from the videos to their own lives (Textbox 1).

Intervention development stages.

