## Results

The above protocol will undergo an internal pilot with 150 participants to identify and make any final adjustments to the procedure prior to full execution of the trial. Any deviations from the protocol documented in this paper will be explicitly acknowledged in the publication of the trial findings.

Data collected during the internal pilot from beginning recruitment to the T2 survey will constitute interim analyses. Although T3 data will be collected from pilot participants, this will not form the basis of the interim analyses due to time constraints imposed on the project, along with the minimal additional information this follow-up time point would have on the decision to proceed to the main trial. Progression to the main trial, including decisions regarding any modifications to the protocol, will be based on participant retention, intervention adherence, data quality, and preliminary assessment of harm. Predefined criteria for each of these parameters are outlined in Table 2, using a traffic light system (red: major modifications or termination of the trial required; amber: minor modifications to be considered; green: proceed with protocol as is).

The pilot study was completed in September 2021. Following positive results from the pilot trial, recruitment for the main trial began in October 2021. The results from the trial are anticipated to be published by mid-2022.

**Table 2 table2:** Progression criteria.

Criteria	Description	Green	Amber	Red
Participant retention (%)	Participant completion of T1^a^ and T2^b^ surveys	70 or above: continue with main trial	50-69: consult research team to advise on changes to survey administration protocol	Below 50: the main trial will need to reconsider how surveys are administered
Intervention adherence, n (%)	Participants viewing all 6 intervention videos	80 or above: continue with main trial	60-79: consult research team to advise on changes to intervention delivery	Below 60: the main trial will need to reconsider how intervention is delivered
Data quality, n (%)	Accurate completion of survey attention checks	80 or above: continue with main trial	60-79: consult research team on possible changes to survey instructions	Below 60: reconsider survey completion protocol

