However, these noteworthy strengths come at a cost. Most notably, the intervention will be accurately created for use on a single-user software platform (Qualtrics) to objectively measure adherence for the trial. Consideration was given to delivering the trial on social media; however, this would have significantly limited individual-level adherence data, even if the research was conducted via a private Facebook group (eg, this would have allowed tracking of still images at the individual level, but not individual-level adherence to watching the videos from start to finish). As such, the approach described in this paper was deemed an appropriate first step in ensuring intervention effectiveness under a somewhat controlled environment where adherence could be tracked. This decision reduces the study’s ecological validity in that it will not be displayed to participants on the same platform as it will be when disseminated. When delivered on social media, there may be the additive effect of collaborative and cooperative learning [99], with young women posting responses publicly, as well as potentially liking and commenting on others’ responses, in contrast to the didactic fashion to be used in the trial. Note that when disseminated, all public responses will be monitored, with any inappropriate or unhelpful comments removed by moderators. This additional element of having the intervention housed on social media will not be evaluated in the trial described here, but future work could look to explore the impact of this additional element.

If found to be effective, *Warna-Warni Waktu* is a relatively inexpensive, scalable public health intervention to reduce body dissatisfaction among young Indonesian women. It could provide a blueprint for the adoption of this intervention format and modality for other countries and cultural contexts. The intervention’s novelty, accessibility, and acceptability among young women are key strengths of the intervention to date; the effectiveness results from this RCT will be invaluable to guide dissemination efforts across social media platforms in Indonesia.

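### Counting a video as watched on minimum page dwell time alone can overstate reported adherence, and the mean engagement time is open to distortion by a few idle pages

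*Protocol article*

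**What the plan says.** The Measures section states: "Intervention adherence will be measured objectively through dwell time spent on the Qualtrics page that contains the video and via participant responses to the activities". Table 1 (Intervention adherence) turns this into six metrics. Metric 1 counts a participant as having watched a video if "dwell time on the Qualtrics page hosting each video is equal to or longer than the length of the video". Metric 2 counts her as having watched the series if "dwell time on all 6 Qualtrics pages hosting videos is equal to or longer than the length of each video". Metric 3, the average number of videos watched, follows from the same rule. Metrics 4 and 5 count completed activities. Metric 6 is the "average length of time spent engaging with the intervention (ie, watching videos and completing activities) over the 6-day period". No maximum, playback event or inactivity check is given for any of these.

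Under Participant Recruitment and Procedure, each daily link runs in this order: state ratings, video, state ratings again, activity, and finally an item in which "participants will be asked to report on the strength of their internet connectivity while watching the video". Neither the second set of ratings nor the connectivity item enters the rule for watched.

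Study Design gives a reliable participant-level adherence record as the reason for delivering the trial in Qualtrics. The Discussion says that a private Facebook group could not have tracked "individual-level adherence to watching the videos from start to finish".

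**The concern.** The rule bounds dwell time from below only. Someone who opens the page and puts the phone down, or whose video stalls, passes once enough time has elapsed, and longer inattention makes a pass more certain. Page-open time is thus a necessary sign of viewing at normal speed, but not a sufficient one.

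Three things are at stake. The first is the descriptive adherence results (metrics 1 to 3). The second is the time-engaged summary (metric 6), where a mean without a ceiling can be moved by a handful of pages. The third, conditionally, is the exploratory dose-response work under hypothesis 3, where crediting non-viewers would misclassify dose and tend to dilute the association.

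The article fixes this definition itself, so it is not a detail left to the analysis plan. It matters somewhat more than usual because the adherence record is the stated reason for giving up social media delivery.

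**Working it through.** The plan states no figure that depends on this rule, so there is none to reproduce. The check is of direction and then of possible size.

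**Direction.** At normal playback speed, everyone who watches a video in full has dwell time at least equal to its length and passes. A non-viewer passes if her page stays open that long. Let p be the true share who watched and f the share of non-watchers credited through idle or stalled pages. Then:

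measured adherence = p + (1 − p) × f, which is never below p.

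Faster playback could produce a few errors the other way. The documents do not say whether the player allows it.

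**Size, metrics 1 to 3.** Both p and f are assumptions.

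| True share p | f = 10% | f = 20% | f = 30% | f = 50% |
|---|---|---|---|---|
| 60% | 64% | 68% | 72% | 80% |
| 70% | 73% | 76% | 79% | 85% |

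For example, 0.70 + 0.30 × 0.20 = 0.76. With p = 60% and f = 20%, 0.60 / 0.68 = 88% of those credited actually watched.

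**Size, metric 6.** The denominator comes from The Intervention section, which gives "6 videos between 4 and 5 minutes each" and 18 activities of about 2 to 10 minutes.

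- Videos: 6 × 4 to 6 × 5 = 24 to 30 minutes.
- Activities: 18 × 2 to 18 × 10 = 36 to 180 minutes.
- Full engagement: 60 to 210 minutes.

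If a share s of participants each add m idle minutes on one page, the mean rises by s × m. Both inputs are assumptions, as is building metric 6 from page times.

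| s | m (minutes) | Rise in mean (minutes) | Relative to 210 to 60 minutes |
|---|---|---|---|
| 1% | 60 | 0.6 | 0.3% to 1% |
| 5% | 60 | 3 | 1.4% to 5% |
| 2% | 480 | 9.6 | 4.6% to 16% |
| 5% | 480 | 24 | 11% to 40% |

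The median would barely move in any of these rows.

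**Link to hypothesis 3.** The Analysis Plan defines adherence there as a count of days completed from Day 3 to Day 8 and does not mention dwell time. The rule reaches that regression only if completion of a day is later defined by it.

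**The case against.** The case on the other side has real force.

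- **Adherence does not rest on page time alone.** Activity responses are part of the measurement and are reported separately. The Analysis Plan also says that the pre- and post-video state ratings are useful for judging adherence. This stands, but neither source enters the definition of watched in Table 1, so metrics 1 to 3 keep the flaw.
- **Metric 6.** A reader might set the 24-minute rise against video time alone (24 to 30 minutes) and infer that idle pages swamp the metric. That is the wrong denominator, because the metric includes the activities. Against full engagement the rise is 11% to 40%, and that is the most extreme scenario shown.
- **Hypothesis 3.** A reader might infer that wholly unexposed participants fill the top dose group. The text does not support this. Completion of a day is not tied to dwell time, and someone who walks away leaves the later steps of that day's link undone. Being credited with all six videos without watching any would take six idle pages.
- **Pilot.** Table 2 has a criterion for "Participants viewing all 6 intervention videos", with green at 80 or above. One might infer that the go decision was unsound. The article reports no pilot counts, and the pilot finished in September 2021, so nothing shows that the decision was affected and a new definition cannot change it.
- **Start-to-finish viewing.** The Discussion uses that phrase for what Facebook could not track. It says of the chosen approach only that adherence could be tracked, so a claim of full-viewing evidence is implied rather than made outright.
- **A fixed dwell ceiling in the main definition.** The documents offer no basis for any particular multiple of video length. It would still pass shorter idle spells and would exclude some genuine viewers who paused.

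**Conclusion.** The point holds in a limited form. The rule credits open but unwatched pages, so at normal playback speed metrics 1 to 3 are at or above the true values. The direction follows from the rule, but the amount cannot be derived from the documents, and every percentage above rests on assumed idle rates. The mean in metric 6 is sensitive to a few long-open pages, by anything from under a minute to about 24 minutes across the scenarios shown. Dilution of the exploratory dose-response is conditional on how completion of a day is defined. The intention-to-treat comparison of the primary outcome does not use adherence and is untouched. This is a worthwhile and inexpensive improvement to secondary reporting, and no threat to the trial's main conclusion.

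**What to change.** Make these changes in the Table 1 definition and carry them into the full statistical analysis plan, which the article says is still to be written. Record them as a deviation from the published protocol.

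1. Count a video as watched only if dwell time is at least the video length and the state rating after that video was submitted.
2. Add a sensitivity analysis in which pages with very long dwell time, or with a poor-connectivity report, count as not watched. Fix both cut-offs before the adherence data are examined.
3. Report metric 6 as median with IQR.
4. State that the completion count for hypothesis 3 uses the definition in item 1.
5. Describe the log as page dwell time plus responses, not as evidence of viewing from start to finish.

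The cost is wording and a few lines of code on data the trial already collects. The headline adherence figure may fall slightly. In the sensitivity analysis some genuine viewers who paused or buffered will count as not watched. Someone who leaves a page idle and later returns to give the rating will still pass item 1, which is why item 2 is needed.
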